### Sample size

A previously published study observed that the complication rate of robotic-assisted colorectal surgery is 17% [12]. According to the retrospective analysis in the medical record system at our institution, the complication rate of traditional robotic-assisted surgery is around 15%. As for the non-inferiority margin, no published studies can be referenced to our knowledge. After a close discussion with the investigators involved in this trial, the margin was set to 10%. We assume that this trial has 80% power (1-β) to detect the complication rate difference between the experimental and control group and a one-sided significance level of 0.025(α = 0.025). Accordingly, 402 participants in total are needed (201 per group). Considering that the overall dropout rate is 20%, we calculated that 503 participants should be enrolled in the study. Finally, 550 participants were recruited in this trial. The sample size was calculated using PASS 11 (version 11.0.7).

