### Randomization and blinding

Stratified block randomization was performed by the Division of Data Management with a block size of 4. The assignment list was generated by a computer program in a block of four and was stratified by cT stage and hospital, which will be sent to the corresponding collaborators of each hospital via e-mail. Participants will then be randomly assigned to an experimental and control group with a 1:1 ratio according to the assignment list. The Division of Data Management will be blinded to the medical data except cT stage and hospital to avoid nonrandom allocation. The patients and the surgeons will not be blind to the allocation.

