### Statistical analysis

Non-inferiority analysis of primary outcomes will be performed in the per-protocol population using the chi-squared test with a one-sided significance level of 0.025, in which the power to detect the surgical complication rate difference is 0.8. The per-protocol population refers to cases that completed the corresponding treatment in each group. All analyses will be performed using SPSS 22.0 (IBM, USA). Both primary and secondary outcomes will be analyzed in accordance with the per-protocol principle. Subgroup analyses will be performed on these variables: gender (between male and female), approach (between vagina and rectum), and cT stage. Unadjusted *p* values will be reported but the number of declared subgroups analyses will be specified in all publications. Multiplicative interaction analysis will be applied, as appropriate.

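### Randomisation is stratified by cT stage and hospital but the stated primary test is not; if these factors are prognostic the test is slightly conservative, so stratifying is a minor efficiency gain

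*Protocol article*

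**What the plan says.** In the protocol article, under Randomization and blinding: "The assignment list was generated by a computer program in a block of four and was stratified by cT stage and hospital". Allocation is 1:1.

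Under Statistical analysis, "Non-inferiority analysis of primary outcomes will be performed in the per-protocol population", "using the chi-squared test with a one-sided significance level of 0.025". No stratified version of the test, no weighting and no covariate is named. cT stage comes back only in the list of subgroup variables, "gender (between male and female), approach (between vagina and rectum), and cT stage". Hospital does not appear in that section at all, and no other section brings either factor into the primary comparison.

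The word unstratified is not used. A pooled 2×2 comparison is simply the plain reading of a chi-squared test named without qualification.

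**The concern.** Blocking within hospital and cT stage forces the arms to be nearly equal on those factors, so differences between strata contribute little to the observed difference between arms. A pooled test does not use this. It estimates the variance as if each arm were one homogeneous binomial sample. If complication rates differ between the seven hospitals or between cT stages, the pooled standard error is larger than the design warrants, and some precision that the randomisation paid for goes unused.

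What is at stake is efficiency: a slightly lower chance of showing non-inferiority when it is true. The choice of test is written into the article, so this is a comment on a stated method and not on a detail left to an analysis plan that is not shown.

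**Working it through.** **Inputs from the article.** Sample size section: control complication rate 15%, margin 10 points, one-sided α 0.025, power 80%, 201 per group (402), 503 after 20% dropout, 550 enrolled. Table 1: one hospital with 130 patients and six with 70 (130 + 6 × 70 = 550). **Assumptions:** 15% in both arms, since no separate rate is given for RN; between-stratum spread and number of cT levels, since neither is stated. The article does not say how the margin enters the chi-squared test, so the calculations use the matching risk-difference comparison with the 10-point margin.

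**1. The plan's own figure.** n per arm = 2 × 0.15 × 0.85 × (1.96 + 0.8416)² / 0.10² = 0.255 × 7.849 / 0.01 = 200.1, rounded up to 201. 402 / 0.8 = 502.5, rounded up to 503. Both reproduce with an unstratified formula, so the sizing does not rely on the strata.

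**2. Formula for the effect of stratifying.** Let s be the standard deviation of the complication rate across the strata and v = 0.1275 − s². With n = 201 per arm:
- pooled SE = √(2 × 0.1275 / n) = 0.0356, 95% half-width 6.98 points;
- stratified SE = √(2v / n);
- stratified power = Φ(0.10 / √(2v/n) − 1.96);
- power of the pooled test = Φ((0.10 − 1.96 × 0.0356) / √(2v/n));
- true one-sided α of the pooled test = 1 − Φ(1.96 × √(0.1275 / v)).

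| s (points) | pooled SE too large by | stratified half-width | power, pooled | power, stratified | n per arm, stratified | true α, pooled |
|---|---|---|---|---|---|---|
| 0 | 0% | 6.98 | 80.2% | 80.2% | 201 | 0.0250 |
| 3 | 0.4% | 6.96 | 80.3% | 80.4% | 199 | 0.0246 |
| 5 | 1.0% | 6.91 | 80.4% | 80.9% | 197 | 0.0239 |
| 7 | 2.0% | 6.85 | 80.6% | 81.7% | 193 | 0.0228 |
| 10 | 4.2% | 6.70 | 81.1% | 83.3% | 185 | 0.0206 |

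**3. Simulation in the trial's layout.** Seven hospitals sized as in Table 1; three cT levels with assumed shares 15/30/55% and shifts −5/0/+3 points; 20% loss; hospital rates drawn from a normal distribution; Mantel-Haenszel risk difference with Sato variance; 6,000 runs per setting.

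| between-hospital SD (points) | mean SE, pooled | mean SE, stratified | power, pooled | power, stratified |
|---|---|---|---|---|
| 3 | 0.0347 | 0.0347 | 82.4% | 82.2% |
| 5 | 0.0347 | 0.0345 | 82.9% | 83.2% |
| 8 | 0.0347 | 0.0342 | 81.8% | 82.6% |
| 10 | 0.0348 | 0.0339 | 82.2% | 83.6% |

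At SD 10 the ratio is 0.0348 / 0.0339 = 1.027 and the power difference is 83.6 − 82.2 = 1.4 points. With no between-hospital variation, a similar run of 3,000 trials gave 82.1% pooled and 81.6% stratified, which is no gain.

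The simulated gains are below the formula's for three reasons. Seven drawn rates carry on average only 1 − Σw² of the nominal variance, where Σw² = (130/550)² + 6 × (70/550)² = 0.153. Negative draws are truncated. Small cells cost the stratified estimate a little.

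**4. False non-inferiority.** With fixed stratum rates, an assumed two cT levels, about 204 per arm and a true difference of 10 points (40,000 runs), the pooled test's one-sided error was 0.0263 with no spread and 0.0201 with hospital rates running from about 2% to 32%. The stratified test gave 0.0259 and 0.0243. The small excess over 0.025 at zero spread is shared by both methods, so it comes from the normal approximation and not from ignoring the strata.

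**5. Sparse cells.** T1 to T3 are eligible, so there may be 7 × 3 = 21 cells. A 70-patient hospital with 20% loss and a 15% cT share has 70 × 0.8 × 0.15 = 8.4 patients in that cell, about 4 per arm and 4.2 × 0.15 = 0.6 events per arm.

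**The case against.** The strongest reply is that nothing is lost unless the strata are prognostic, and the article offers no evidence on that. Entry is narrow (ECOG 0 or 1, T1-3N0M0) and every surgeon does more than 100 robotic gastrointestinal operations a year, which argues against a large spread. The larger gains need extreme assumptions: around a 15% mean, 20% of draws at SD 8 and 39% at SD 10 contain a hospital with a negative rate. At SD 5 or less the gain is about zero. Any error is on the safe side, and enrolment has slack, since 550 × 0.8 = 440 evaluable against 402 needed. All of this stands, and it sets the severity. It does not remove the mismatch between design and stated analysis, which costs little to close.

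A reader might also infer that stratifying would protect the result from the exclusions that the per-protocol analysis invites: the withdrawal criteria, the photographic adherence check and the planned 20% loss. The documents do not support that. A stratified estimate removes imbalance on hospital and cT stage in the patients analysed. If patients leave one arm for reasons tied to their outcome, the bias remains within each stratum.

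**Conclusion.** The point holds as a minor efficiency improvement. The mismatch is certain from the text; its cost is conditional. Over assumed between-hospital standard deviations of 0 to 10 points, the simulated pooled standard error is about 0 to 3% too large and about 0 to 1.5 power points are lost. The idealised formula puts the ceiling at 4.2% and 83.3 − 81.1, about 2 points, if the realised spread across strata is a full 10 points.

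Two stronger readings are tempting and fail. One is that the pooled standard error is too large as a matter of fact: with no prognostic effect the two analyses agree. The other is that the primary conclusion or its power is compromised: ignoring the strata does not raise false non-inferiority, and the stated 80% power holds at 201 per arm in every setting in the first table.

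The size rests on a 15% rate in both arms and on invented stratum rates and cT shares. The direction does not depend on the particular values chosen.

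**What to change.** In the Statistical analysis section, for the primary outcome, replace the unqualified chi-squared test with a risk difference (RN minus RA) stratified by cT stage and hospital, using Mantel-Haenszel weights with Sato or stratified Miettinen-Nurminen limits. Declare non-inferiority if the one-sided 97.5% upper limit is below 10 points.

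Fix the sparse-cell rule before the data are analysed: pool cT levels within a hospital, with the trigger stated, for example when a cell has no patients in one arm.

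The cost is a few sentences and a few lines of code. The strata are recorded at randomisation, so no data or patients are added. The statement that all analyses use SPSS 22.0 should be widened if that software does not provide the chosen limits. The text should not present the change as a remedy for per-protocol exclusions.

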### Withdrawal criteria

The withdrawal criteria are as follows:
Postoperative pathology confirmed the tumor is pT4 or N1–2;Intraoperative exploration or postoperative pathology confirmed distant metastasis;During the treatment period, the patients received other therapies other than this study regimen;Intraoperative exploration requires combined visceral resection;Postoperative pathology confirmed non-rectal adenocarcinoma; andAfter being enrolled in the study, the patients were required to be withdrawn from the study cohort for various reasons.

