### Intervention

Patients will be randomly allocated into the RA (traditional robotic-assisted surgery) group and RN (Robotic natural orifice specimen extraction surgery) group. The specimen will be extracted through the rectum and vagina [13, 14]. In terms of female participants, in principle, extracting the specimen through rectum will be prioritized. This is a surgical trial; there are no strategies for patients to improve adherence. All the surgeons included in this study perform more than 100 robotic gastrointestinal surgeries a year. In order to make surgeons adhere to intervention protocol, critical surgical nodes will be photographed. And these photos will be submitted to the Division of Data Management. The Research Committee will check the surgical quality. The non-adherent cases will be excluded from per-protocol analysis. The schedule of this trial is shown in Fig. 2.

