### Primary outcomes

Incidence of surgical complications 30 days postoperative. The classification of surgical complications will be classified using the Clavien-Dindo system.

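### Every outcome is analysed only in patients who completed the assigned operation, with no as-randomised set, so randomisation does not protect the non-inferiority comparison; bias is possible, its direction and size unknown

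*Protocol article*

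**What the plan says.** The Statistical analysis section of the protocol article fixes the set for the primary test: "Non-inferiority analysis of primary outcomes will be performed in the per-protocol population using the chi-squared test with a one-sided significance level of 0.025". It defines that set: "The per-protocol population refers to cases that completed the corresponding treatment in each group". It then extends the rule to every endpoint: "Both primary and secondary outcomes will be analyzed in accordance with the per-protocol principle". No intention-to-treat, full or as-randomised set is named anywhere in the article, even as a supporting analysis.

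Two other sections remove patients after randomisation:

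- **Intervention.** Photographs of key surgical steps are checked for quality, and "The non-adherent cases will be excluded from per-protocol analysis".
- **Withdrawal criteria.** Patients leave on pathological findings, on intraoperative findings (for example "Intraoperative exploration requires combined visceral resection"), and under an open-ended clause for unspecified reasons.

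Under Randomization and blinding, "The patients and the surgeons will not be blind to the allocation". The primary outcome is "Incidence of surgical complications 30 days postoperative".

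**The concern.** Whether a patient completes the assigned operation is known only after randomisation, and it may be linked to the outcome. If extraction through rectum or vagina fails and the abdomen must be opened to remove the specimen, the RN operation as assigned has not been completed. On the article's definition the patient then leaves the analysis, together with any complication. RA removes the specimen through a planned 5 to 6 cm midline incision, so it cannot fail in this way.

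The groups compared are therefore not the groups randomised. If failed extractions are the harder cases, the observed RN complication rate is too low and an RN procedure that is truly worse by the full margin passes more often than 2.5% of the time. The secondary outcomes rest on the same selected patients. The article's question is whether choosing robotic NOSES is safe, and that choice is made before anyone knows whether extraction will succeed.

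This is a rule the article states, not a detail it leaves to an analysis plan.

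**Working it through.** **Inputs from the Sample size section.** Complication rate 15%, margin 10 points, one-sided alpha 0.025, power 80%, 201 per group, 20% dropout, 550 recruited.

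**Reproducing the plan's figure.** With unpooled variance, n per arm = 2 × 0.15 × 0.85 × (1.960 + 0.842)² / 0.10² = 200.1, rounded up to 201 (402 in total). Then 402 / 0.80 = 502.5, so 503. Both agree with the article, and the sample size is not at issue here.

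**Inputs that are assumptions.** The article gives neither the share of failed extractions nor their complication rate. Let c be the share of RN dropped and q the complication rate among them. Set the true as-randomised rates at the margin: 25% in RN, 15% in RA. Take 220 per arm (550 × 0.80 / 2) before these exclusions. RA loses nobody unless stated.

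**Formula.** Per-protocol RN rate = (0.25 − c × q) / (1 − c). False non-inferiority is the exact binomial probability that the upper 95% limit of the difference (unpooled) lies below 10 points.

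| Scenario | RN rate per protocol | Difference, points | False non-inferiority |
|---|---|---|---|
| No exclusions | 25.0% | 10.0 | 2.6% |
| c = 5%, q = 45% | (0.25 − 0.0225)/0.95 = 23.9% | 8.9 | 4.8% |
| c = 10%, q = 60% | (0.25 − 0.06)/0.90 = 21.1% | 6.1 | 18.0% |
| c = 5% or 10%, q = 25% (RN average) | 25.0% | 10.0 | 2.6% |
| c = 5%, q = 15% | (0.25 − 0.0075)/0.95 = 25.5% | 10.5 | 1.9% |
| c = 10%, q = 15% | (0.25 − 0.015)/0.90 = 26.1% | 11.1 | 1.3% |
| RN: c = 10%, q = 60%; RA: 10% dropped, 50% complicated | 21.1% (RA: (0.15 − 0.05)/0.90 = 11.1%) | 10.0 | 2.7% |

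The error rises only if dropped RN cases do worse than the RN average and RA does not lose comparable cases. It is unchanged or falls otherwise.

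**Power as randomised.** Power = Φ[(0.10 − (p_RN − 0.15)) / SE − 1.96], where SE = √(p_RN(1 − p_RN)/n + 0.15 × 0.85/n).

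- 15% in both arms: 83.6% with 220 per arm and 90.7% with 275 per arm (all 550 evaluable).
- Completers at 15%, c = 5%, q = 45%: p_RN = 0.95 × 0.15 + 0.05 × 0.45 = 16.5%. With 275 per arm, SE = 0.0311 and power is about 78%.
- Completers at 15%, c = 10%, q = 60%: p_RN = 0.90 × 0.15 + 0.10 × 0.60 = 19.5%. SE = 0.0322 and power is about 40%.

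**The case against.** The strongest defence is that per-protocol analysis is customary in non-inferiority trials, because an as-randomised analysis can dilute a real difference. That is a fair point. If RN completers have 25%, converted cases have 15% and RA has 15%, the as-randomised error with 275 per arm is 3.6% (5% converted) to 4.9% (10% converted). This supports keeping the per-protocol set. It does not support using it alone.

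A reader might infer that RA has no way of leaving the analysis. The text does not say so: completion is required in each group, and neither the photograph check nor the withdrawal criteria are limited to RN. What stands is narrower, namely that RN has one additional way to fail. The Exclusion criteria also remove tumours too large to be drawn out through anus or vagina, which should prevent some failed extractions before randomisation.

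A reader might also infer that the plan is biased towards success. That needs failed extractions to carry more complications than the RN average, and the article has no figure for this. The 18.0% comes from the worst corner of an assumed range with no RA exclusions.

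The analyst blinded to allocation (Data collection and management) does not answer the point, because patients leave the set before the analysis.

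**Conclusion.** The concern holds in a limited form. As written, all conclusions rest on a set defined by events after randomisation, in an open-label trial, with no as-randomised analysis beside it. Loss of the randomised comparison follows from the text alone.

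Bias towards non-inferiority is plausible, but its direction and size cannot be read from the article. Under the stated assumptions false non-inferiority is 4.8% to 18.0%; under others, equally open on the text, it is 1.3% to 2.7%. These figures show that the rule can matter. They do not estimate what will happen in this trial.

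**What to change.** - Add an analysis of all randomised patients as assigned, keeping failed or converted extractions in RN. The Recruitment and participants section asks whether data may be used after withdrawal, so data on withdrawn patients are included as consent allows.
- Claim non-inferiority only if the upper limit of the difference is below 10 points in both this set and the per-protocol set.
- Analyse secondary outcomes in the as-randomised set, with per-protocol as support.
- Settle the photograph-based adherence exclusions before complication data are seen.

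**Cost.** The change is to analysis wording, plus 30-day complication data on patients who would otherwise be dropped; some of these may be unavailable where consent is refused. Power is the real cost and should be stated. The 90.7% with 275 per arm applies only if the as-randomised RN rate is 15% and all 550 are evaluable. With completers at 15% and 5–10% converting at 45–60% complications, power is about 78% to 40%. That fall reflects a truly higher RN rate, which the trial ought to detect, but the sponsor should know it in advance.

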### Traditional robotic-assisted surgery

Patients will be performed traditional robotic-assisted colorectal resection following the total mesorectal excision(TME) principle. All patients are intubated under general anesthesia in the lithotomy position. We employ the 5-hole trocar layout. The navel is used to explore the abdominal cavity, and two operation holes are established on the right and left lower abdomen. The peritoneum is incised at the junction of the sigmoid mesocolon and the pelvis to find the inferior mesenteric vessels. Clamp and cut off the inferior mesenteric vessels while the left colonic vessels are kept as far as possible, with the surrounding lymph nodes being thoroughly cleaned. After entering the Toldts gap, the naked sigmoid colon and rectum are freely exposed outward and downward, and the rectum is cut off with a linear cutter stapler and cartridge approximately 3 to 5 cm under the lower edge of the tumor. The abdomen is then entered layer-by-layer and the incision protector is placed through a midline abdominal incision with a length of 5 to 6 cm. Afterward, the proximal intestine is removed, and a specimen is cut off from the colonic mesocolon 10 to 15 cm upper the tumor. After disinfecting the cut edge, the intestine is placed into the stapler holder and undergoes an external purse-string suture into the abdominal cavity. Pneumoperitoneum is then reestablished, and the stump of the intestine is flushed from the anus. Then, the stapler is placed, and the end-to-end anastomosis is completed under the endoscope. Finally, a rubber drainage tube is placed and fixed on the left abdominal wall next to the anastomosis from the trocar hole.

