### Robotic natural orifice specimen extraction surgery via rectum

Patients will receive robotic colorectal resection with natural orifice specimen extraction surgeries through the rectum or vagina. After general anesthesia, the 5-hole method is used in the lithotomy position with the right thigh placed horizontally. After cutting the first incision in the mesorectum at about 3–5 cm below the sacral headland, the Toldts gap is then entered, freeing the root of the inferior mesenteric vessels and separating the bare inferior mesenteric vessels layer-by-layer with a pre-cut line, which is then ligated and cut. The mesorectum is freed, after which the avascular area of the sigmoid mesocolon is opened, while the rectal mesentery is freed downward and outward to the bifurcation of the left common iliac and separated downward along the anterior iliac gap. After the inferior hypogastric plexus is exposed, an ultrasonic knife is used to carry out separation at a uniform speed along the nerve surface. This process simultaneously frees the left and right sides of the rectum 3–5 cm below the tumor. After determining the location of the tumor, intestinal wall nakedness is performed within a range of about 3 cm within 5 cm below the tumor. The sigmoid colon is then exposed for about 2 cm, after which the sigmoid mesenteric vessels are ligated and cut and the pre-cut line is determined. The assistant then fully expands and washes the anus, and an iodine gauze ball is placed under the tumor to indicate the intestinal incision. After the intestinal incision is made, the assistant places the stapler holder from the anus into the abdominal cavity through the intestinal incision for backup. At the same time, a longitudinal incision is made on the intestinal wall above the tumor. The iodine gauze is sterilized and inserted into the intestine through the longitudinal incision. The intestinal canal is then cut and closed with a linear cutter stapler and cartridge above the longitudinal incision. The rectum is subsequently severed using an ultrasonic knife at the incision below the tumor. The assistant then places the specimen into the protector through the anus by the oval forceps outside and clamps the specimen out of the anus using the oval forceps. The cutter stapler and cartridge close the stump of the distal rectum canal, and the annular stapler is then inserted through the anus. The stapler holder is then docked with the body to complete the end-to-end anastomosis. Finally, a water injection test is performed to determine the presence of bleeding or leakage, after which a rubber drainage tube is placed in the pelvic cavity.

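### Extraction approach (vagina or rectum) exists only in the RN arm, so it cannot be a treatment-effect subgroup, and the contrast left within RN is non-randomised and confounded by sex

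*Protocol article*

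**What the plan says.** The Statistical analysis section of the protocol article names three subgroup variables in one sentence: "Subgroup analyses will be performed on these variables: gender (between male and female), approach (between vagina and rectum), and cT stage". It then says that subgroup p values will be reported unadjusted, and adds: "Multiplicative interaction analysis will be applied, as appropriate". It makes no exception or special provision for approach.

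The surgical sections define how specimens leave the body in each arm.

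- **Control arm (RA).** Under Traditional robotic-assisted surgery: "the incision protector is placed through a midline abdominal incision with a length of 5 to 6 cm". No other extraction route is described for this arm.
- **Experimental arm (RN).** Under Robotic natural orifice specimen extraction surgery via rectum: "Patients will receive robotic colorectal resection with natural orifice specimen extraction surgeries through the rectum or vagina". The section that follows it describes the vaginal technique.
- **Choice of route in women.** Under Intervention: "In terms of female participants, in principle, extracting the specimen through rectum will be prioritized".

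Under Randomization and blinding, the assignment list "was stratified by cT stage and hospital". Neither sex nor route is a stratification factor. The same section says: "The patients and the surgeons will not be blind to the allocation".

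**The concern.** A treatment-effect subgroup asks whether RN compares with RA differently in one kind of patient than in another. The variable must therefore have a value in both arms, and it should not be part of one of the treatments. Gender and cT stage meet both conditions. Approach meets neither: it is a feature of how the RN operation is done, and RA patients have no value for it.

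Since approach appears in the same sentence as two proper baseline subgroups, with interaction analysis announced for the set, a reader of the results would take it as the same kind of evidence. Its nearest computable substitute is a comparison of two self-selected parts of one arm that differ in sex by construction. The primary outcome is surgical complications, and the Introduction itself lists vaginal and anal strain injury among the risks of NOSES, so a result by route will attract attention. A difference between men and women could be reported as a difference between routes.

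**Working it through.** **1. Arm sizes, from the plan's own figures.** The article gives no number for the approach subgroup, so the only stated figure to reproduce is the overall sample size. The inputs are in the Sample size section: 15% complications (taken here as equal in both arms), a 10-point margin, one-sided alpha 0.025 and 80% power.

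- n per arm = 2 × 0.15 × 0.85 × (1.960 + 0.842)² / 0.10² = 200.1 to 200.2, rounded up to 201. The total is 402, as stated.
- With 20% dropout: 402 / 0.80 = 502.5, rounded up to 503, as stated.
- Planned enrolment from Table 1: 130 + 6 × 70 = 550, or 275 per arm at 1:1.

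**2. The arm-by-approach table.** Filled from the surgical sections, with f the proportion of women in RN, v the proportion of RN women with vaginal extraction, and n the size of the RN arm:

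| Arm | Vagina | Rectum | Abdominal incision |
|---|---|---|---|
| RN | n × f × v | n × (1 − f × v) | 0 |
| RA | 0 | 0 | all |

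The RN row takes every patient as treated by the described technique. The RN-versus-RA difference within the vaginal column needs an RA complication rate in that column. There are no RA patients in it, and the same holds for the rectal column. An interaction is a contrast between those two within-column effects, so it cannot be estimated either. This holds on any scale and at any sample size.

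**3. What can be computed: vagina versus rectum within RN.** The article gives neither f nor v. Taking f from 0.40 to 0.50 and v from 0.10 to 0.50 as assumptions:

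- Vaginal group at n = 275: from 275 × 0.40 × 0.10 = 11 to 275 × 0.50 × 0.50 = 69.
- Vaginal group at n = 201: from 201 × 0.40 × 0.10 = 8 to 201 × 0.50 × 0.50 = 50.

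**4. The sex imbalance.** The vaginal group is 100% women under any assumption. Men are a share s = (1 − f) / (1 − f × v) of the rectal group:

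| f | v | s |
|---|---|---|
| 0.40 | 0.10 | 0.60 / 0.96 = 0.625 |
| 0.40 | 0.50 | 0.60 / 0.80 = 0.75 |
| 0.50 | 0.10 | 0.50 / 0.95 = 0.53 |
| 0.50 | 0.50 | 0.50 / 0.75 = 0.67 |

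**5. What that does to the contrast.** Suppose route has no effect, RN women have complication rate w whichever route is used, and RN men have rate m. The vaginal rate is w. The rectal rate is s × m + (1 − s) × w. The difference is s × (w − m). Each percentage point of true difference between the sexes would thus appear as about 0.53 to 0.75 points of apparent route effect. Restricting the comparison to RN women sets s to 0 and removes this term.

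**6. What restriction does not remove.** The rectal route is prioritised in women only in principle, and the Intervention section states no rule for departing from it. Women who have vaginal extraction are a selected group even among RN women, and the surgeons who operate know the allocation.

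**The case against.** The strongest reply is that the sentence never says approach will be crossed with treatment arm. Read literally, it contrasts two routes, which can be done within RN, and interaction analysis is promised only as appropriate. The choice of comparison set and model is the kind of detail that a journal article leaves to the full protocol or analysis plan. Subgroup results also drive no decision here, and the number of declared subgroup analyses will be disclosed.

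Part of this stands. The article does not commit itself to an arm-by-approach term, and a within-RN comparison is possible. But that reading does not rescue the analysis as listed: it compares an all-female group with a mixed-sex one and does not label the result as non-randomised. No analysis plan can fill the empty RA cells unless an intended route was recorded in both arms before randomisation, and the article describes no such record.

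A reader might infer three stronger points, which the article does not support.

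- **That route is decided after allocation.** This is plausible, since route is not a stratification factor and surgeons are unblinded, but no section says when the choice is made. The Inclusion and Exclusion criteria, with a specimen-size limit for the transvaginal procedure and gynaecological exclusions, suggest some assessment beforehand. The RA cells are empty either way.
- **That the contrast is confounded by tumour bulk.** The article gives no reason for leaving the rectal route, and the eligibility criteria limit size. Confounding by sex is documented; confounding by bulk is conjecture.
- **That a multiplicative interaction is wrong because the margin is an absolute difference.** The 10-point margin belongs to the primary test. No subgroup is tested against it, so the scale is a matter of preference.

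**Conclusion.** The point holds in this form: approach has no counterpart in the RA arm, so neither a treatment effect by approach nor an arm-by-approach interaction can be estimated. The within-RN contrast that remains is non-randomised and confounded by sex. The first part follows from the surgical descriptions alone and needs no assumption about numbers or timing. In the second part, the all-female vaginal group and the presence of RN men in the rectal group are certain. The group sizes and the share of men rest on the assumed ranges for the proportion of women and for vaginal use.

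The consequence is limited to one declared subgroup analysis. The gender and cT stage subgroups, the primary non-inferiority comparison and the sample size are untouched. The change is worth making before results are seen, because afterwards a choice of comparison set could look driven by the data.

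**What to change.** Remove approach from the list of treatment-effect subgroups and from the interaction tests, leaving gender and cT stage. Add a sentence to this effect: complication rates by actual extraction route will be reported for women in the RN arm only, as an exploratory, non-randomised comparison, with an interval estimate and no claim about the effect of RN against RA. Comparing each RN route with the whole RA arm would be no substitute, since the vaginal group would then be set against an arm not restricted to women.

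Optionally, if enrolment still permits, record before randomisation the route that would be intended under RN for every woman in both arms, and use that as the subgroup variable among women. This asks for a surgical judgement on each woman, not just a form field. It may come too late: Trial status anticipates recruitment from February 2020, and the Sample size section already speaks of recruitment in the past tense.

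The wording change costs nothing in patients or in power for the primary outcome. Its price is a smaller and less precise route comparison. Under the assumptions above and 275 per arm, it would rest on about 110 to 138 RN women (275 × 0.40 to 275 × 0.50), of whom 11 to 69 would have vaginal extraction.
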